#### Deqi sensation assessment

2.6.4

Following the completion of both trials, participants will be assessed for the types and intensity of Deqi sensations using the Modified Massachusetts General Hospital Acupuncture Sensation Scale-Chinese version (C-MMASS) (21). The C-MMASS evaluates 12 specific types of sensations: soreness, pain, pressure, heaviness, distension, tingling, numbness, dull ache, warmth, cold, throbbing, and other sensations. The intensity of each sensation will be rated on a scale from 0 to 10, where 0 indicates no sensation, 1–3 represents mild intensity, 4–6 moderate intensity, 7–9 severe intensity, and 10 signifies the maximum tolerable intensity.

### Data management and statistical analysis

2.7

#### Data preprocessing

2.7.1

The preprocessing of magnetic resonance imaging (MRI) data will involve format conversion using the dcm2niigui software, followed by subsequent preprocessing steps performed with the Statistical Parametric Mapping (SPM12) toolbox on the MATLAB R2021A platform. The workflow will include the following procedures: (1) To ensure data stability, images from the first five time points will be excluded during preprocessing. (2) All remaining scanned images will then be aligned to the middle image and corrected for head motion. (3) During motion correction, volumes exhibiting head displacement with 3D translation of >1.5 mm or 3D rotation >1.5° will be deleted (22). (4) For spatial registration, each patient’s T1-weighted images will be co-registered with their corresponding functional images. (5) The images will then be uniformly segmented and resampled. The retained data will undergo spatial normalization into Montreal Neurological Institute (MNI) space. (6) Finally, spatial smoothing will be applied using a Gaussian kernel with a full width at half maximum of 6 mm.

#### Functional connectivity and network analysis

2.7.2

Resting-state functional connectivity (FC) analysis was employed to investigate the synchronized activity between brain regions (23, 24). Specifically, we utilized seed-based correlation analysis, a widely used method to quantify FC between specific regions of interest (25). Following standard resting-state fMRI preprocessing, the mean time series will be extracted from a predefined seed region of interest (ROI). Whole-brain connectivity maps will be generated by computing Pearson’s correlation coefficients between the seed time series and the time series of every other voxel in the brain. The resulting correlation coefficients (*r*-values) will be converted to *Z*-scores using Fisher’s *Z*-transformation to normalize their distribution for subsequent group-level statistical analysis.

The resulting connectivity matrices were then used to construct brain networks where nodes were defined according to the Dosenbach-160 atlas (26), and edges represented the significant FC between node pairs. Subsequently, graph-theoretical analysis was performed to characterize the topological properties of these networks using measures such as clustering coefficient and characteristic path length (27, 28). All analyses were carried out using the GRETNA toolbox (29). Using these nodes and the Fisher’s *Z*-transformed connectivity strengths as weighted edges, we will construct individual functional brain networks for each subject and time point. Key graph-theoretic metrics, including global efficiency (quantifying global integration), local efficiency (quantifying local specialization and fault tolerance), and nodal degree/strength (quantifying regional influence), will be computed from these networks across a range of connection densities to characterize their topological organization robustly.

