**Methods:**

We designed a randomized, single-blind, controlled trial. To achieve high statistical power and generalizability, 250 healthy participants will be enrolled. Each participant will undergo acupuncture at one of seven predefined acupoints (verum) and its corresponding non-acupoint (sham control) in two separate sessions, with a 1-week interval. Each session includes: (1) resting-state fMRI before and after needle manipulation, and (2) task-fMRI during the manipulation. The primary outcomes are fMRI-derived brain activity and functional connectivity patterns. Blinding assessment and the Modified Massachusetts General Hospital Acupuncture Sensation Scale-Chinese version (C-MMASS) will be collected to evaluate the credibility of sham control and the Deqi sensation.

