#### Pre- vs. post-acupuncture changes

3.2.1

Following verum acupuncture, significant reorganization of resting-state functional connectivity occurs compared to sham acupuncture. This includes weakened connectivity within the default mode network (DMN), suggesting that the brain may remain less prone to mind-wandering even at rest; enhanced coupling between the salience network (SN) and the central executive network (CEN), indicating a potential improvement in the brain’s ability to flexibly switch between internal Deqi sensation and external tasks; and reduced hyper-connectivity among pain-related regions such as S1, S2, thalamus, and anterior insula, which may underlie its long-term analgesic effects.

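### No stated connectivity analysis measures all three network changes the article expects versus sham, and no stated correction covers this primary outcome

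*Protocol article*

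**What the plan says.** The abstract of the protocol article sets the outcome: "The primary outcomes are fMRI-derived brain activity and functional connectivity patterns".

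Section 2.7.2 (Functional connectivity and network analysis) describes two routes.

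- **Seed route.** "the mean time series will be extracted from a predefined seed region of interest (ROI", and maps are made by "computing Pearson’s correlation coefficients between the seed time series and the time series of every other voxel in the brain". The values are then Fisher-Z transformed.
- **Node route.** Networks on the Dosenbach-160 atlas, with Fisher-Z connectivity as weighted edges, are built for each participant and time point. The measures named for them are clustering coefficient, characteristic path length, global and local efficiency, and nodal degree or strength.

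Section 3.2.1 (Pre- vs. post-acupuncture changes) says that after verum acupuncture "significant reorganization of resting-state functional connectivity occurs compared to sham acupuncture", and lists three components:

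1. "weakened connectivity within the default mode network (DMN"
2. "enhanced coupling between the salience network (SN) and the central executive network (CEN"
3. "reduced hyper-connectivity among pain-related regions such as S1, S2, thalamus, and anterior insula"

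Section 2.7.3 (Statistical analysis) gives, for resting-state data before and after needling, a paired t-test of functional activity. Its voxel and cluster threshold is stated for the task fMRI analysis. The other imaging corrections belong to the common-effects analysis (2.7.4) and to functional decoding (2.7.5).

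**The concern.** A seed map contains only connections that have the seed at one end. The three expected changes lie in different parts of the brain's connectivity, so the described analysis and the expected findings do not match. If the analysis is run as described, at least one expected change has no measurement behind it. If seeds are added until each change can be examined, there are at least three chances of a positive finding, with no order among them and no stated adjustment.

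The comparison is also incomplete. The changes are expected relative to sham, but the resting-state test named is pre versus post. A significant change after verum alongside a non-significant change after sham does not show that the two changes differ.

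**Working it through.** **Step 1. Which seed covers which expected change (2.7.2 against 3.2.1).**

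| Seed placed in | Within-DMN | SN-CEN | S1, S2, thalamus, anterior insula |
|---|---|---|---|
| DMN | only the seed's own DMN connections | no | no |
| SN or CEN | no | the seed's own connections | no, unless the seed is the anterior insula |
| Anterior insula, if taken to represent the SN | no | the seed's own connections | 3 of 6 pairs |
| S1, S2 or thalamus | no | no | 3 of 6 pairs |

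Four regions form 4 × 3 / 2 = 6 pairs, and a seed in one of them touches 3. No row covers all three columns, so the result does not depend on which seed is chosen.

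**Step 2. Whether the node route fills the gap.** Efficiency, clustering and path length summarise topology. Nodal degree or strength sums a node's connections to all others. None of them is mean connectivity within the DMN, between SN and CEN, or among the four regions. The weighted 160-node matrices contain the edges needed, but the article does not plan those summaries.

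The text also introduces the connectivity matrices as if they came out of the seed step. A seed-to-voxel map does not yield a node-by-node matrix, which is a separate computation.

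**Step 3. Error control.** The plan gives no figure to reproduce here: no resting-state alpha, and no power calculation for connectivity. The sample-size rationale in 2.3 concerns activation at a single voxel. For illustration, assume each of three claims is tested at two-sided 5%.

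- Independent claims: 1 − 0.95³ = 0.143.
- Equal correlation of 0.3, 0.5 or 0.8 between the claims, by simulation of normal test statistics: 0.14, 0.13 and 0.10.
- The expectations in 3.2.1 have a direction. Counting only false positives in that direction (2.5% per claim): 1 − 0.975³ = 0.073 if independent, and 0.07, 0.06 and 0.05 at correlations 0.3, 0.5 and 0.8 between the direction-aligned statistics.

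**Step 4. Price of adjusting.** With 30 participants per acupoint (2.3), a one-sample t-test on a within-participant difference, two-sided, has 80% power for a standardised effect of 0.53 at level 0.05. At Holm's strictest step, 0.05 / 3 = 0.0167, the figure is 0.62. The unit is the standard deviation of the difference tested.

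**The case against.** **The seed is called predefined, and a journal article need not list coordinates.** This stands. A reader might infer that the missing seed name is itself the defect, or that the seed will be chosen after the results are seen. The article supports neither. The point rests on step 1, which holds for any seed.

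**Section 2.7.2 does not limit the study to one seed.** Partly right. The sentence describes how a seed map is made, and the one before it speaks of regions in the plural. Several seeds may be intended. In that case the mismatch shrinks, but the number of unadjusted claims becomes the issue.

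**The data can answer all three questions.** True, through the node matrices. A reader might conclude that the expectations are untestable, which would be too strong. What is missing is a stated measure, not the data.

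**Section 3.2.1 gives anticipated results in a mapping study, not declared hypotheses.** This also stands, and if all three changes were required jointly there would be no family-wise inflation. However, it is where the article sets out the expected resting-state changes versus sham, and it says nothing about joint success.

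**The repeated-measures ANOVA in 2.7.3 might supply the sham comparison.** Its factors are not given, and its follow-up is described for activation patterns. The resting-state comparison listed is pre versus post.

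**The error figures are assumed.** Correct. The 5% level is not in the article, and a whole-brain map is not a single test.

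**Conclusion.** The point holds in a limited form. No stated connectivity analysis measures all three changes expected versus sham, the stated resting-state test lacks the sham comparison, and none of the stated corrections covers resting-state connectivity although it is a primary outcome. The first conclusion follows from what a seed map and the listed graph metrics contain, and needs no numerical assumption.

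The size is illustrative. Within one acupoint, three unadjusted claims give a family-wise error of about 0.10 to 0.14, or about 0.05 to 0.07 if only the predicted direction counts. Both ranges assume two-sided 5% per claim and correlations from 0.8 down to 0.

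A reader might multiply the three claims over seven acupoints and report 1 − 0.95²¹ = 0.66 as the error rate of this analysis. Most of that comes from the number of acupoints, a separate question, and it presumes that any one positive result among 21 would be claimed as success. The article does not say so. Nor does it establish that the DMN must be the primary network: section 3.1.2 concerns DMN suppression during the task, and the Discussion pairs the DMN with the salience network for ST36 only.

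**What to change.** In sections 2.7.2 and 2.7.3:

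1. From the Fisher-Z 160-node matrices already planned, compute three averages per participant, session and time point: mean within-DMN connectivity, mean SN-CEN connectivity, and mean connectivity among the S1, S2, thalamus and anterior insula nodes. Fix the assignment of nodes to networks in advance; the article does not show one.
2. Test each average as the within-participant difference (verum post − verum pre) − (sham post − sham pre).
3. Apply Holm over the three within each acupoint.
4. Either adjust across the seven acupoints or state that error is controlled per acupoint. Under the second choice, the chance of at least one false positive over seven separate groups can reach 1 − 0.95⁷ = 0.30, and readers should be told so.
5. Label the seed maps and graph metrics exploratory.
6. State that the node matrix is computed separately from the seed maps.

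The cost is wording, a node list and a short script, with no new scans. The downside is a stricter threshold per claim (detectable standardised effect up to 0.62 instead of 0.53 with 30 participants). Network averages may also miss focal effects, which the exploratory seed maps could still show.

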#### Statistical analysis

2.7.3

Neuroimaging analyses will be conducted using the SPM12 toolbox on the MATLAB platform. First, one-sample *t*-tests will be performed to identify brain activation patterns associated with verum acupuncture (at true acupoints) and sham acupuncture (at non-acupoints). Subsequently, repeated-measures analysis of variance (ANOVA) will be applied. If statistically significant effects are detected, paired-sample t-tests will be conducted between the two groups to identify differential brain activation patterns between true acupoints and non-acupoints. Additionally, paired-sample *t*-tests will be performed to compare: (1) Resting-state functional activity pre- versus post-acupuncture; (2) Resting-state activity (pre-acupuncture) versus task-based activity (during acupuncture). A voxel-wise threshold of *p* < 0.005 with a false discovery rate-corrected cluster level of *p* < 0.05 was applied in the task fMRI analysis. Significant activation clusters will be visualized and localized using the xjView, MRIcron, and BrainNet Viewer toolboxes within the MATLAB platform.

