**Discussion:**

This study is novel in its comprehensive approach to mapping the neural correlates of multiple acupoints within a single, rigorous design. We anticipate that our results will provide the first systematic characterization of the “acupoint-brain functional network” map, elucidating both common activation patterns across acupoints and acupoint-specific differential responses. This will significantly contribute to understanding the functional neuroanatomy of acupuncture and provide high-level evidence for its mechanism of action, ultimately helping to bridge the gap between traditional practice and modern neuroscience.

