To address these limitations, the present study employs a rigorous, single-acupoint design under a well-controlled, task-based fMRI paradigm. We focus on a therapeutically significant and commonly used acupoint to precisely investigate its distinct impact on functional brain network dynamics. Our objectives are twofold: (1) to isolate the specific central effects of a defined acupoint from non-specific responses using a robust sham-control design, and (2) to interpret these findings within the established framework of CNS network modulation, thereby contributing to a more precise understanding of acupuncture’s neural mechanisms and its potential applications in cognitive regulation.

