### Sample size

2.3

Currently, there are no standardized criteria for determining sample sizes in MRI studies, as they are often constrained by practical considerations such as scanning time and cost. Based on an efficiency analysis of sample size estimation in MRI research, a previous study indicated that approximately 12 participants are required to achieve 80% power at the single-voxel level for typical activation effects (19). In line with this reference and considering the study design, we set a sample size of 30 participants per acupuncture point. Each volunteer will undergo both verum and sham acupuncture at the same acupoint, resulting in a total of 210 experimental sessions. To account for potential data loss due to head motion or participant dropout, we plan to enroll a total of 250 subjects.

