### Randomization, allocation concealment, and blinding

2.4

In this study, participants will be randomly assigned to one of the seven acupoint groups. The randomization sequence is generated using SPSS 26.0 software, and the allocation scheme is concealed using opaque sealed envelopes. Upon participant enrollment, the allocation will be revealed by sequentially opening the envelopes to determine the assigned acupoint for acupuncture. The blinding procedure involves three aspects: first, participants are blinded to the specific acupoints used in the trial; they are only informed that the acupoints are located in the distal limbs. Second, radiologists, due to their professional constraints, are unaware of the specific acupoints and their significance, ensuring the objectivity of the scanning process. Third, image processors are blinded to the participants’ group assignments, ensuring the objectivity of the image processing.

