#### Sham acupuncture group

2.5.2

Non-acupoints are localized at 1.5 cm lateral to the corresponding verum acupoints (Table 1), outside meridian trajectories and neurovascular bundles, avoiding tender points and hair follicles (Figure 3). Identical opaque, non-metallic sponge pads, as used in the verum group, will be placed on the skin surrounding the target area after disinfection. Blunt-tipped placebo needles (Suzhou Acupuncture & Moxibustion Appliance Co., Ltd., China; 0.25 × 30 mm) will be vertically placed on the skin surface without penetration, maintaining slight tactile pressure. Hence, the Deqi experience of the participants will not be overemphasized. Except locations of acupoints and needle penetration, the manipulation procedures and course will be the same with the verum acupuncture group (Figure 4).

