#### Common brain effects of acupoints, pain-related brain regions, and differential brain effects

2.7.4

Analyses of common brain effects elicited by acupoint stimulation will be performed using GingerALE software (Version 3.0.2, http://brainmap.org/ale) with cluster-level family-wise error (FWE) correction. The following parameters will be applied: 5,000 permutations for statistical testing, a cluster-forming threshold of *p* < 0.001, and a statistical significance threshold of *p* < 0.05 (cluster-level FWE corrected) (30). Additionally, a predefined pain-related brain map (derived from the Neurosynth database, https://neurosynth.org) will be used to evaluate spatial overlap between acupoint-induced activation clusters and pain-associated brain regions. The overlap analysis will adopt a statistical significance threshold of *p* < 0.05.

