## Discussion

4

In this study, we will examine whether acupoints engage both shared and distinct brain regions during neural regulation, with the specificity of these regions potentially underlying their unique therapeutic functions.

Our aim is to establish a bridge between traditional medicine and modern medicine through this research. Based on traditional Chinese medicine theory, LI4 (Hegu) is primarily used for pain relief and disorders of the head and face, with strong regulatory effects on Qi and blood. PC6 (Neiguan) harmonizes the stomach, alleviates nausea and vomiting, calms the Shen, and addresses cardiac and chest discomfort. ST36 (Zusanli) tonifies the whole body, strengthens the spleen and stomach, improves digestion and energy, and supports immunity. SP6 (Sanyinjiao), where the spleen, liver, and kidney meridians converge, is key in treating gynecological and urogenital disorders and nourishing blood and Yin. GB34 (Yanglingquan), the influential point for tendons, is essential for musculoskeletal conditions and lateral body pain. KI3 (Taixi), the kidney source point, tonifies kidney essence (Jing) and addresses deficiencies in both kidney Yin and Yang, which are foundational in aging and chronic disease. LR3 (Taichong), the liver source point, soothes the liver, promotes Qi flow, alleviates stress and emotional constraint, and treats disorders related to liver Qi stagnation. For instance, we anticipate that acupuncture at ST36 will significantly modulate the DMN and the salience network. Notably, DMN activity is closely linked to self-referential processing, introspection, and impairments of the gut-brain axis in gastrointestinal diseases (31, 32). Thus, we expect that our results may provide a neuroscientific basis for the action of ST36: by regulating the DMN and visceral sensory regions, ST36 could help restore homeostasis of the gut-brain axis, offering a modern biological correlate to its traditional role in “harmonizing the stomach and spleen.”

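### The aims promise acupoint-specific and common responses, but no between-acupoint contrast is specified, and common effects are assigned to a coordinate-based meta-analysis tool

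*Protocol article*

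**What the plan says.** **Aims.** The Discussion paragraph of the Abstract anticipates a map "elucidating both common activation patterns across acupoints and acupoint-specific differential responses". Section 4 says "we will examine whether acupoints engage both shared and distinct brain regions during neural regulation". The Introduction frames the objective differently, around a single point against sham: "to isolate the specific central effects of a defined acupoint from non-specific responses using a robust sham-control design".

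**Design.** Under section 2.4, "participants will be randomly assigned to one of the seven acupoint groups". Each person receives verum and sham at that one point. Verum against sham is therefore a within-person comparison, and acupoint against acupoint is a between-person comparison. Section 2.3 states: "we set a sample size of 30 participants per acupuncture point".

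**Analysis.** Section 2.7.3 lists one-sample tests for verum and for sham, then a repeated-measures ANOVA whose factors are not given. If the ANOVA is significant, "paired-sample t-tests will be conducted between the two groups to identify differential brain activation patterns between true acupoints and non-acupoints". The remaining tests are paired: pre against post, and rest against task. Section 2.7.4 has differential brain effects in its heading, but its text covers only two things. One is an overlap with a pain map. The other is the common-effects analysis: "Analyses of common brain effects elicited by acupoint stimulation will be performed using GingerALE software". The coordinates or experiments to be entered into GingerALE are not described.

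**The concern.** The question in the Abstract and section 4 is whether acupoints differ from one another and what they share. None of the contrasts named in section 2.7.3 compares one acupoint with another. The verum–sham contrast cannot stand in for that comparison. It asks whether needling at a point differs from its own control, and that control changes two things at once: "Except locations of acupoints and needle penetration, the manipulation procedures and course will be the same with the verum acupuncture group".

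If the text is followed as it stands, specificity will be inferred by laying separate acupoint maps side by side and noting where one is significant and another is not. That is not a test of a difference. Points with the same true effect can look specific simply because each map has limited power.

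The common-effects half has a related weakness. Activation likelihood estimation tests whether reported coordinates converge. It is built for situations where only coordinates are available, and it does not use effect size or sub-threshold signal. This trial will hold every participant's images from one protocol, so a more direct and more sensitive analysis is open to it.

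**Working it through.** **Inputs from the article.** Seven acupoints (2.4, 2.5); 30 participants per acupoint (2.3), so 7 × 30 = 210 participants; voxel threshold p<0.005 for task fMRI (2.7.3). The article states no between-acupoint figure to reproduce, and it gives no effect size or SD.

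**Assumptions.** A one-sided t-contrast; the same true standardised effect d at all seven points; one voxel; the cluster-level step ignored. The groups contain different people, so their maps are independent.

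**Step 1: power of one map.** With n=30 and 29 degrees of freedom the one-sided 0.005 critical value is 2.756, so p = P(T > 2.756), where T is noncentral t with noncentrality d√30. At d=0.5 the noncentrality is 0.5 × 5.477 = 2.739 and p = 0.503.

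**Step 2: chance that some but not all seven maps pass.** This is 1 − p⁷ − (1 − p)⁷, which is largest at p = 0.5.

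| d (assumed) | power p | none pass | all pass | some but not all |
|---|---|---|---|---|
| 0.3 | 15% | 31% | <0.1% | 69% |
| 0.4 | 31% | 8% | <0.1% | 92% |
| 0.5 | 50% | 0.8% | 0.8% | 98% |
| 0.6 | 70% | <0.1% | 8% | 92% |
| 0.8 | 94% | <0.1% | 65% | 35% |
| 0.9 | 98% | <0.1% | 87% | 13% |

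Reading p<0.005 as two-sided (critical value 3.038), the last column becomes 53%, 83%, 97%, 97%, 53% and 24%.

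**Step 3: the article's only power anchor.** Section 2.3 cites about 12 participants for 80% power at a single voxel, without an alpha. Solving for d with n=12 and carrying it to n=30 at one-sided 0.005:

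- anchor at 0.05 one-sided: d = 0.77, power 92%, disagreement 46%
- anchor at 0.05 two-sided: d = 0.89, power 98%, disagreement 15%
- anchor at 0.005 one-sided: d = 1.17, power above 99.9%, disagreement 0.2%

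**Step 4: shared effects.** At d=0.4 a single map passes with probability 0.305, so on average 7 × 0.305 = 2.1 of seven maps pass. A pooled one-sample test in 210 participants has power above 99%.

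**Step 5: detectable effects (80% power, one-sided 0.005).**

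- one acupoint, n=30: d = 0.66
- pooled, n=210: d = 0.24
- two acupoints, 30 v 30 (noncentrality d√(30/2)): d = 0.91, before any multiplicity correction

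**Step 6: multiplicity.** Seven points give 7 × 6 / 2 = 21 pairs. Testing all of them uncorrected at 0.05 gives 1 − 0.95²¹ = 66% family-wise error if they are treated as independent.

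**The case against.** The strongest reply is that this is a condensed article. ANOVA factors and contrast lists commonly sit in a full protocol or analysis plan, and the unnamed factors may well include acupoint. That stands in part: a reader might infer that no between-acupoint test is planned at all, and the text does not support going that far. It supports only that none is specified. The gap is still more than ordinary condensation. The article goes down to software versions, permutation counts and cluster thresholds, names a single follow-up to the ANOVA, and gives the differential analysis a heading with nothing under it.

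A reader might also infer that the headline question cannot be answered. That is wrong: acupoint is randomised and individual images will be available, so the right test can be run on the planned data.

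It is also tempting to say that GingerALE would see just seven thresholded peak lists. The article does not describe the input, so the figure of about two maps in seven describes separate thresholded maps and is not a prediction of what GingerALE would find. The method also smooths foci in space and does not require agreement at the same voxel. That it works from coordinates is intrinsic to it, so the preference for participant-level models remains.

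On size, 98% is close to the mathematical maximum of the formula and should not be quoted as typical. Under the article's own anchor the disagreement runs from 46% down to 0.2%. That anchor concerns activation, however, and verum-minus-sham effects may be smaller.

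Finally, the Introduction lists only a single-acupoint, verum–sham objective, and sections 3.1.1, 3.1.2 and 3.5 use *common* and *differential* in that sense. The paired test does serve that sense. This shows that the aims and terms are inconsistent; it does not remove the acupoint-against-acupoint aim in the Abstract and section 4.

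**Conclusion.** The point holds in this form: the stated analysis does not match the stated aim. The article promises acupoint-specific differences without specifying a between-acupoint contrast, and it assigns common effects to a coordinate-based tool when participant-level data will be available.

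If specificity is read from separate maps, points with identical effects would look different at a given voxel in about 69% to 98% of cases for d from 0.3 to 0.6, falling to 35% at 0.8 and 13% at 0.9. These figures rest on assumed effect sizes, one-sided testing, a single voxel and no cluster step. The risk is therefore large for small to moderate effects and small for very large ones. The documents do not say which applies.

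**What to change.** - **Section 2.7.3.** Name the ANOVA factors: acupoint (seven levels, between participants) by condition (verum or sham, within participants), with visit order. Claim acupoint-specific effects only from the acupoint-by-condition interaction on participant-level verum-minus-sham images, with multiplicity-corrected follow-up of the 21 pairs.
- **Section 2.7.4.** Replace GingerALE for common effects with participant-level models. Report the pooled average effect and a seven-group conjunction as separate claims: the pooled effect is where the sensitivity comes from, and the conjunction is more conservative. Either supply the differential method that the heading announces or point to section 2.7.3.
- **Aims and terms.** Give *common* and *differential* one meaning each. At present they refer to verum against sham in sections 3.1.1, 3.1.2 and 3.5, and to acupoint against acupoint in the Abstract and section 4. Reconcile both with the single-acupoint objective in the Introduction.

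**Cost.** Wording and model set-up, on the same data. The real price is sensitivity: a pairwise between-acupoint contrast needs d of about 0.91 (30 v 30, one-sided 0.005), and more after correction, so fewer specificity claims should be expected.
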